### Secondary outcome measures

Secondary outcome measures collected on the 'follow-up children' will include the number of absence episodes due to respiratory illness, number of absence episodes due to gastrointestinal illness, length of illness episode, length of absence episode, and number of household members who become ill within one week of the participating child's illness onset (Table 1). An illness will be defined as respiratory or gastrointestinal using the definitions applied in a previous trial [13]. A respiratory illness will be defined as an acute illness that includes at least one of the following symptoms: runny nose, stuffy or blocked nose, cough, fever or chills, sore throat, or sneezing. A gastrointestinal illness will be defined as an acute illness that includes at least two watery or much looser than normal bowel movements and stools over a 24 hour period and/or vomiting. The definition of a new episode of absence due to either respiratory or gastrointestinal illness will be defined in the same way as for the primary outcome measure. The length of an absence episode will be defined as the number of days a child was absent from school for a particular episode. The length of the illness episode will be defined as the number of days between the first and last day of absence. For children who are absent on only a Monday

or only a Friday, we will define the length of the episode as two days.

Secondary outcome measures collected on all children from the school roll include the number of absence episodes and the length of an absence episode.

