### **Trial objectives**

The primary objective of the trial is to establish if the provision of hand sanitisers in primary schools in the South Island of NZ, in addition to an education session on hand hygiene, reduces the incidence rate of absence episodes due to illness in children. Secondary objectives

include whether hand sanitisers are effective in reducing the (i) incidence rate of respiratory illness absence episodes, (ii) incidence rate of gastrointestinal illness absence episodes, (iii) average length of illness episode, (iv) incidence rate of absence for any reason, (v) average length of absence episode, (vi) average number of household members who become ill within one week of the participating child's illness onset. We will examine if the intervention is associated with any skin reactions. We will also undertake a cost-effectiveness analysis, providing incremental cost-effectiveness ratios for the cost per absence episode due to illness avoided, the cost per absence attributable to illness, and the cost per days of work lost for parents/guardians (hereafter referred to as parents). We will also conduct a cost-benefit analysis, with the benefits being measured using parents' reported willingness-to-pay (WTP).

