#### **Trial outcomes**

##### **Primary outcome measure**

The primary outcome measure for this trial is the number of absence episodes due to *any* illness over 20 weeks; excluding injuries and infestation (head lice and scabies) (Table 1). Absence due to *any* illness has been selected as our primary outcome, in preference to absences due to infectious illness because of difficulties in accurately diagnosing the illness through interviews with the children's parents. The definition of a new episode of absence due to illness has been variously defined between trials. For example, Guinan et al [11] defined a new episode of absence due to illness as one in which there was a lapse of at least five days between a previous period of absence due to illness. Other trials have defined a new episode of absence due to illness as one where the child is absent for at least one day in a given week [10]. We will define a new episode of absence due to illness as one in which there have been at least three days with no absences due to illness. So, for example, if a child is absent from school on Friday, present on Monday, and absent on Tuesday; this will constitute two absences. However, if a child is absent from school on a Tuesday, present on Wednesday, and absent again on Thursday; this will constitute one absence. While there is no theoretical justification for any particular definition for a new episode of absence due to illness, an absence period of at least three days has the advantage of classifying a child who is absent on a Friday and Monday as having only one absence episode, and further, this definition has been used previously [21].

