**Table 1 Outcome measures**

| Outcome                                                                                               | Collected by                            | Timing of collection                                              | Source              |
|-------------------------------------------------------------------------------------------------------|-----------------------------------------|-------------------------------------------------------------------|---------------------|
| Primary outcome                                                                                |                                         |                                                                   |                     |
| Number of absence episodes due to any illness                                           | Telephone interview                     | 8 - 9 days after the date of the first day of absence from school | Parents of children |
| Secondary outcomes                                                                             |                                         |                                                                   |                     |
| 'Follow-up children'                                                                           |                                         |                                                                   |                     |
| Number of absence episodes due to respiratory illness                                                 | Telephone interview                     | 8 - 9 days after the date of the first day of absence from school | Parents of children |
| Number of absence episodes due to gastrointestinal illness                                            | Telephone interview                     | 8 - 9 days after the date of the first day of absence from school | Parents of children |
| Length of illness episode                                                                             | Telephone interview                     | 8 - 9 days after the date of the first day of absence from school | Parents of children |
| Length of absence episode                                                                             | Telephone interview                     | 8 - 9 days after the date of the first day of absence from school | Parents of children |

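### The length-of-illness definition gives a two-day value only to Monday-only and Friday-only absences and leaves end-day counting open, so scores depend on weekday and a Friday-only absence scores at least as long as Thursday-Friday

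*Protocol*

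**What the plan says.** The Protocol lists "average length of illness episode" as secondary objective (iii) under Trial objectives. Secondary outcome measures gives the general rule: "The length of the illness episode will be defined as the number of days between the first and last day of absence". The exception follows directly: "For children who are absent on only a Monday", "or only a Friday, we will define the length of the episode as two days". No reason is given for it.

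The same section defines the companion outcome separately: "The length of an absence episode will be defined as the number of days a child was absent from school for a particular episode". Table 1 obtains both lengths for the follow-up children from a parent interview timed at "8 - 9 days after the date of the first day of absence from school".

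Under Primary outcome measure, a new episode starts once "there have been at least three days with no absences due to illness". One stated merit of that choice is "classifying a child who is absent on a Friday and Monday as having only one absence episode".

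**The concern.** A measure of duration should give equal values to equal absences, and it should score an absence above any shorter absence that it contains. This rule does neither reliably. The two-day value goes only to single-day absences on a Monday or a Friday. A one-day absence therefore scores differently by weekday, and adding Thursday to a Friday absence does not raise the score.

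Because end-day counting is not stated, two analysts following the text could also produce different values for most episodes. At stake is the meaning of the mean illness length reported for objective (iii), and some precision in comparing the arms on it.

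**Working it through.** **Inputs.** These are the general rule and the exception, both from Secondary outcome measures. The two-day value is a definition, so there is no derived figure to reproduce. The general rule alone would give Monday-only and Friday-only absences 0 or 1.

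**Two readings of the general rule.**
- Literal difference: length = last date − first date.
- Inclusive count: length = last date − first date + 1.

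**Scores with the exception applied (calendar days).**

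| Absence pattern | School days absent | Literal | Inclusive |
|---|---|---|---|
| Tuesday, Wednesday or Thursday only | 1 | 0 | 1 |
| Monday only or Friday only | 1 | 2 | 2 |
| Any two consecutive school days in one week (e.g. Thursday-Friday) | 2 | 1 | 2 |
| Tuesday and Thursday | 2 | 2 | 3 |
| Friday and following Monday | 2 | 3 | 4 |
| Monday-Wednesday or Wednesday-Friday | 3 | 2 | 3 |

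**Comparisons.**
- Friday-only against Thursday-Friday: both adjoin the same weekend and the second contains the first. The scores are 2 v 2 (inclusive) or 2 v 1 (literal).
- Friday-only against Wednesday-Friday: 2 v 3 (inclusive) or 2 v 2 (literal).
- Friday-only against Tuesday-only, both one day: 2 v 1 (inclusive) or 2 v 0 (literal).

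Without the exception, every one-day absence scores 1 (inclusive) or 0 (literal), and every consecutive two-day absence scores 2 or 1. One-day absences then rank strictly below two-day ones on both readings.

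**Effect on the mean.** The Protocol does not give the weekday distribution or the share of single-day episodes, so both are assumed.
- If single-day absences are spread evenly over five weekdays, 2/5 = 40% receive the exception.
- Mean single-day score, inclusive: (2 + 1 + 1 + 1 + 2)/5 = 1.4, against 1.0 without the exception, a shift of 0.4.
- Mean single-day score, literal: (2 + 0 + 0 + 0 + 2)/5 = 0.8, against 0.0, a shift of 0.8.
- If half of all episodes are single-day, the overall mean shifts by 0.5 × 0.4 = 0.2 day (inclusive) or 0.5 × 0.8 = 0.4 day (literal).
- If the single-day share is 30% to 70%, the shift is 0.12 to 0.28 day (inclusive) or 0.24 to 0.56 day (literal).

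**Effect on the between-arm difference.** The shift is common to both arms and largely cancels. If the arms differed by 5 percentage points in single-day share (assumption), the difference in means would change by 0.05 × 0.4 = 0.02 day (inclusive) or 0.05 × 0.8 = 0.04 day (literal).

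**The case against.** The best defence is that the outcome is illness, not absence. A child away only on a Friday or a Monday may also have been ill on the adjoining weekend day, which no school record shows. On that view two days means one school day plus one weekend day, which also points to inclusive counting. The order is then never reversed for these patterns; the fault is ties and unequal one-day scores. Part of this stands. The purpose is plausible though unstated, the inclusive reading is the more natural one, and the span of absence is not a gold standard for illness length. It does not rescue the rule, because Thursday-Friday adjoins the same weekend and gets no allowance.

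A second objection is that the effect is small and non-differential. That also stands.

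A reader might infer more than the text supports:
- **Length of absence, objective (v), is affected too.** It has its own definition as a count of days absent, and the exception follows the illness-length sentence, so its position ties it to illness.
- **The cost results inherit the error.** The cost-effectiveness ratios under Trial objectives concern episodes, absences and work days lost, and Economic evaluation uses missed work time and willingness to pay. Nothing is said to be computed from this score.
- **Long episodes are truncated at the interview.** Table 1 fixes when the call is made. It does not say that later absence days are discarded, and the number of episodes still running at that point is not given.

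**Conclusion.** The definition is internally inconsistent as written. On either reading, one-day absences score differently by weekday, and a Friday-only absence is not scored below a Thursday-Friday absence that contains it. A true reversal needs the literal difference reading and holds for consecutive two-day absences. On the inclusive reading the fault is a tie. Gapped two-day absences score higher than a Friday-only absence on the inclusive reading.

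The consequence is measurement error in one secondary outcome and a reported mean that depends partly on which weekday short absences fall. The mean moves by about 0.2 day (inclusive) or 0.4 day (literal) if half of episodes are single-day and evenly spread over weekdays. The rule is identical in both arms, so it does not by itself favour either. It leaves the primary outcome, length of absence episode and the economic outcomes untouched. It is still worth correcting, because this is a stated rule for a named outcome and applying it faithfully would reproduce the fault.

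**What to change.** Define length of illness episode as last absence date minus first absence date plus 1, for every episode. Then treat weekends in one of two consistent ways:

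- drop the Monday/Friday exception; or
- give the same allowance to every episode that adjoins a weekend. With one extra day, for example, Friday-only scores 2 and Thursday-Friday scores 3. The text should then also say what happens when an episode adjoins a weekend at both ends, such as Monday to Friday.

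Either choice removes the inconsistency. The first measures span of absence; the second keeps an attempt to capture unseen weekend illness.

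As a minor addition, where a follow-up child is still absent at the day 8-9 call, complete the last absence date from the weekly school absence data.

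The cost is a few sentences of definition. The absence dates are already being collected, and neither sample size nor data collection changes.

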### Adverse events

Following the intervention period, telephone interviews of parents of the 'follow-up children' will be undertaken to collect information on the presence of any skin reactions which may have occurred during the intervention period including: dryness, redness, flakiness, itchiness, eczema, and any other skin reactions.

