#### **Blinding**

It is not possible to blind the children, school administrative staff, or the school liaison research assistants. However, the investigators not involved in the running of the trial (JM, RA, MP, CB), outcome assessors, and statistician (JM) will be blinded until the analysis is completed.

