##### **Intervention group**

Intervention schools will have the in-class session described above to discuss hand hygiene and to be instructed in the use of the hand sanitiser during term 1, 2009 (March and April 2009). No-touch dispensers will be fitted in all classrooms during the first school holidays in 2009 (April 2009). The hand sanitiser will be at least 60% alcohol.

Children will be able to use the sanitiser at any time they wish, but teachers will be asked to ensure that the children use the hand sanitiser after coughing/sneezing/blowing their nose, and as they leave for morning break and for the lunch break. These times have been chosen for two reasons. First, this will allow the slightly unpleasant smell of the sanitiser (following use by the whole class) to disperse before the children return to the classrooms. Second, break times are when transmission is likely to be higher from children touching one another.

The hand sanitisers will be placed in classrooms to ensure that there will be some teacher oversight of their use, minimising the chances of children playing with the dispensers and sanitiser, and of children getting squirted in the eyes or mouth.

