#### **Timing of recruitment, intervention, and follow-up**

School principals will be contacted for potential inclusion in the trial in November 2008. Parents of randomly selected children will be mailed an information sheet and consent form during term 1, March 2009, to seek consent to participate in post-absence interviews.

All schools will be given a single health education session on hand hygiene during term 1, (March and April) 2009. Hand sanitisers will be present in the intervention schools during terms 2 and 3, 27 April to 25 September 2009.

Absence information will be collected for a total of twenty school weeks from the first week of term 2, 27 April 2009. Research assistants will collect absence information from each school weekly. Parents of randomly selected children who have consented to participate in the post-absence interviews will be telephoned eight - nine days after the date of the first day of absence from school.

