| Number of household members who become ill within one week of the participating child's illness onset | Telephone interview                     | 8 - 9 days after the date of the first day of absence from school | Parents of children |
| All children                                                                                   |                                         |                                                                   |                     |
| Number of absence episodes for any reason                                                             | Liaison research assistant  | Weekly                                                            | School roll         |
| Length of absence episode                                                                             | Liaison research assistant  | Weekly                                                            | School roll         |
| Adverse events                                                                                 |                                         |                                                                   |                     |
| Skin reactions                                                                            | Telephone interview                     | Following the intervention period                                 | Parents of children |

 'Follow-up children' only.

 Parents will not be telephoned where it is clear that the child was not unwell (for example, on a holiday, attended a funeral, etc).

 Through contact with school staff or by extracting the data in person.

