#### **Ethical review**

The New Zealand Multi-Region Health and Disability Ethics Committee provided approval for the trial on 13 March 2009 (MEC/09/01/005).

C-RCTs offer additional ethical complexity compared to individually randomised participant trials [32-34], particularly concerning informed consent of individuals. In this trial, the school principals will act as the "gatekeepers"; providing written consent for the school to participate in the trial, be randomised, and potentially receive the hand sanitisers. Parents of all children in the schools allocated to the hand sanitiser group will be contacted with an information sheet explaining the study and informed that hand sanitisers will be fitted in each classroom in their child's school. Parents will be informed that they can opt their child out of using the hand sanitiser at any stage throughout the trial. Parents of the randomly selected sub-sample of children (including children in the intervention and control groups) will be asked to provide written informed consent for the researchers to conduct post-absence interviews with them.

Anonymised data on absences from all children will be collected from the school rolls. Consent for this data collection will not be obtained from parents. Parents of the children in the intervention group will be informed that this data will be collected, through the information sheet described above. Parents of the children in the control group will not be informed of the anonymised data collection.

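### The only safety outcome is specific neither to the hands nor to new onset and rests on recall by parents who know the allocation, so neither a null nor a positive result could readily be attributed to the sanitiser

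*Protocol*

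**What the plan says.** The protocol sets a comparative safety question under Trial objectives: "We will examine if the intervention is associated with any skin reactions". Skin reactions are the only adverse event in Table 1 and in the Adverse events section.

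- **What is asked.** The item is "the presence of any skin reactions which may have occurred during the intervention period including: dryness, redness, flakiness, itchiness, eczema, and any other skin reactions". No body site, severity, onset or new-versus-existing criterion is given.
- **When and of whom.** "Following the intervention period, telephone interviews of parents of the 'follow-up children' will be undertaken"; Table 1 gives the same timing, "Following the intervention period". No other collection point is described.
- **Period covered.** "Hand sanitisers will be present in the intervention schools during terms 2 and 3, 27 April to 25 September 2009".
- **Baseline.** The section on descriptive analyses at baseline mentions demographic variables and potential confounders without listing them. Skin status is not named.
- **Who knows the allocation.** Under Ethical review, parents in the sanitiser arm are "informed that hand sanitisers will be fitted in each classroom in their child's school" and may opt their child out. Under Blinding, "It is not possible to blind the children, school administrative staff, or the school liaison research assistants"; outcome assessors are blinded.
- **A further hazard.** The Intervention group section explains classroom placement partly as "minimising the chances of children playing with the dispensers and sanitiser, and of children getting squirted in the eyes or mouth". No eye or mouth event is among the adverse events collected.

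**The concern.** A sanitiser acts on the hands, but the item counts a skin complaint anywhere on the body, including eczema, which a child may already have had before term 2. The illness outcomes, by contrast, are asked about 8–9 days after the first day of absence, and respiratory and gastrointestinal illness have explicit symptom definitions. The safety outcome is therefore measured much more loosely than the efficacy outcomes.

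Two different problems follow, and they should be kept apart. Background complaints make a real hand reaction harder to see. Knowledge of the allocation can make intervention parents notice, remember or report more. A null result could then reflect dilution, and a positive one could reflect recall. The trial's one stated safety question would be hard to answer either way.

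The statistical analysis plan cannot repair this later. If hand site and new-or-worsened status are never asked, no analysis can recover them.

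**Working it through.** **The plan's own figures.** The protocol gives no rate, power or sample size for skin reactions. Its primary-outcome figure does reproduce: (1.96 + 0.84)² × (1/2.2 + 1/1.76) / (ln 0.8)² = 161.2 children per arm. The design effect is 1 + 49 × 0.15 = 8.35, and 161.2 × 8.35 / 50 = 26.9, so 27 schools; 27 / 0.8 gives 34 after attrition. None of this bears on skin reactions except the number of children, 27 × 50 = 1,350 per arm.

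**Recall window.** 27 April to 25 September is 151 days, and 151 / 7 = 21.6, so about 22 weeks.

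**Dilution.** Let b be the background risk of the reported event, equal in both arms, and suppose the sanitiser causes a reaction in 5% of otherwise unaffected children. All rates are assumptions. The observed ratio is (b + (1 − b) × 0.05) / b, and the excess risk is (1 − b) × 5%.

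| Outcome | b | Ratio | Excess (points) |
|---|---|---|---|
| Any skin reaction | 10% | 0.145 / 0.10 = 1.45 | 4.5 |
| Any skin reaction | 20% | 0.240 / 0.20 = 1.20 | 4.0 |
| Any skin reaction | 40% | 0.430 / 0.40 = 1.08 | 3.0 |
| New hand reaction | 2% | 0.069 / 0.02 = 3.45 | 4.9 |
| New hand reaction | 5% | 0.0975 / 0.05 = 1.95 | 4.75 |

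**Precision.** This is a second illustration with a different assumed effect: new hand reactions of 2% in control and 5% in intervention schools, plus a background b of other complaints. The risks are b + (1 − b) × 0.02 and b + (1 − b) × 0.05. The effective number per arm is 1,350 / (1 + 49 × ICC), which at an assumed ICC of 0.01 is 1,350 / 1.49 = 906. Power is from a two-sided 5% normal test of two proportions.

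| b | Risks | Ratio | Power, ICC 0 | Power, ICC 0.01 | Power, ICC 0.05 |
|---|---|---|---|---|---|
| 0 | 2.0% vs 5.0% | 2.50 | 99% | 94% | 63% |
| 10% | 11.8% vs 14.5% | 1.23 | 55% | 40% | 20% |
| 20% | 21.6% vs 24.0% | 1.11 | 32% | 23% | 12% |
| 40% | 41.2% vs 43.0% | 1.04 | 16% | 12% | 7% |

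**Recall, with no true effect.** If informed parents report d extra points, the ratio is (b + d) / b. Over b = 20–40% and d = 2–5 points it runs from 0.42 / 0.40 = 1.05 to 0.25 / 0.20 = 1.25. Put as reporting probabilities on a true 20%: if control parents report 70% of complaints and intervention parents 80% or 90%, the reported risks are 14% against 16% or 18%. The false ratios are 1.14 and 1.29, significant with probability about 22% and 64% at ICC 0.01.

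**The case against.** The case on the other side has real force.

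- **Existing eczema is no bias.** A reader might infer that it distorts the comparison. Schools are randomised within region, so earlier skin complaints balance in expectation. They add noise and shrink the ratio. This stands.
- **Nothing shows that the signal is swamped.** A reader might also infer that background complaints and recall together bury a true reaction. The documents give no background rate, and near zero background the loss is small. On the absolute scale most of the excess survives (3.0 to 4.5 points, against 4.75 to 4.9 for hands only); the main cost is precision. Recall by informed parents would more plausibly raise a difference than hide one. This stands too.
- **Silence about baseline is not proof of absence.** The baseline variables are not listed and the interview form is not shown. One can say only that no baseline skin item is described, and it is not certain that long-standing eczema would be counted as occurring in the period.
- **The symptoms are listed one by one.** Dryness could be compared separately from eczema, and the protocol does not prescribe a single pooled outcome. That helps, but it supplies neither hand site nor new onset.
- **Assessors are blinded.** This guards against interviewer bias, but it does nothing about a respondent who knows the allocation.
- **Eye and mouth exposure is a separate matter.** Classroom placement for teacher oversight is a preventive measure. Whether exposures are recorded is a question of completeness and does not support the skin-measurement point.

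**Conclusion.** The point holds in a limited form. The only safety outcome is a parent report of any skin reaction over about 22 weeks, specific neither to the hands nor to new onset, with no baseline skin status described and with intervention respondents aware of the sanitiser.

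Dilution costs precision without biasing the comparison; differential recall is the bias, and it probably acts upwards. How large either would be depends wholly on assumed background, reaction and recall rates, and for power on an assumed ICC and on all 1,350 parents per arm being interviewed. The illustrations show that the loss can be large at plausible inputs, not that it will be. This is a cheap and worthwhile improvement to a safety measure. It is not an error or contradiction in the plan, and it leaves the primary efficacy result untouched.

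**What to change.** In the Adverse events section and Table 1:

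- Keep the symptom list, but ask in both arms about the hands and elsewhere on the body as separate items, and whether each reaction is new or worse since the start of term 2.
- Make new or worsened hand reactions the main safety comparison. Use the 'elsewhere' item as a check on recall: the sanitiser is used on the hands, so a difference elsewhere would point mainly to reporting.
- Add a short item on existing skin problems or eczema to the consent form sent in March 2009, before dispensers are fitted in April. That form already carries a question on the parents' English.
- Ask about eye or mouth exposure in the same end-of-trial interview, in both arms.

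If liaison assistants also note incidents or opt-outs each week in intervention schools, treat this as descriptive monitoring. The assistants are unblinded and the data would come from one arm, so they cannot support a between-arm comparison.

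The cost is a slightly longer consent form and interview, with possibly some priming of parents. Schools are allocated before the form goes out, so some parents may answer the baseline item knowing their arm, though before any exposure. If the interviews were already carried out as described, what can still be done is to report the symptoms separately and state that the result cannot be tied to new reactions of the hands.
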